On the day of Enrollment (Day 0) (2-6 days after the next menses, within 30 days of screening), participants will return to the GCRC. Test results from screening will be reviewed. Urine will be collected for a repeat pregnancy test. If the pregnancy test remains negative, a speculum exam will be performed and the vagina and cervix will be visually inspected. A pH sample from the vaginal wall and a gentle swab for wet mount will be obtained. A vaginal swab will be collected for assessment of vaginal flora and a cytobrush will be obtained to measure immune cell populations. If there is evidence of a clinically detectable genital abnormality (i.e., ulcer, lesion or positive wet mount) appropriate treatment and follow-up will be provided and the participant will be ineligible to participate further at this time. If there is evidence of recent intercourse (sperm visualized on wet mount or positive p30 test), the participant will be ineligible to continue in the study. If the patient is eligible, participants will be randomized to receive Acidform lubricant or HEC gel. The participant will insert one dose of study gel intravaginally under the guidance of the study clinician. A repeat pelvic exam with visual inspection, measurement of vaginal pH and collection of CVL will be performed 2 hours after application of Acidform or HEC gel. Provided that the first dose is well tolerated, the participants will insert subsequent applications twice daily for 13 consecutive days (preferably in the morning and at bedtime) (see Appendix III). Subjects will be instructed and frequently reminded to apply one dose in the morning and a second dose at bedtime. Study gels will be provided in single-use tubes with separate vaginal applicators and the participant will be provided with a study diary to record usage, symptoms and reasons for non-adherence.

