Every effort will be made to bring participants back after 7 and 14 doses of Acidform or HEC. Visits will be scheduled in the GCRC on Day 7 (range, days 5-9) and Day 14 (range, days 12-15). For study visits conducted on Day 7 and 14, subjects will be instructed to apply the morning dose after the study visit is completed. There will be a Final Visit scheduled on Day 21 (range, days 16-21), prior to the anticipated onset of menstruation. A pelvic exam will be performed and vaginal pH will be measured at each visit. CVL samples will be obtained at the Screening Visit, Enrollment Visit (2 hours after the application of Acidform or HEC), and on Days 7, 14, and 21. A cytobrush for measurement of immune cell populations and a vaginal swab for assessment of vaginal flora will be collected at Enrollment (prior to application of Acidform or HEC), Day 14 and Day 21. [name] or [name] will collect one cervical biopsy colposcopically at the Day 14 visit for assessment of epithelial integrity. Participants will be instructed to document symptoms of vulvar or vaginal soreness or pruritus, vaginal bleeding, dysuria, or acts of vaginal penetration in a study diary, which will be provided. Participants will be asked to record information on the number of times they administer study gel, time of each insertion, emergence/resolution of specific symptoms and reasons for non-adherence. Diaries will be reviewed at each visit. Participants will bring used and unused supplies with them to each visit for counting and disposal. Adverse events will be recorded as described in Section 8.0. Subjects will receive $25 at the Screening visit. An additional $25 will be given at Screening if a biopsy is performed. Fifty dollars will be provided at the Enrollment, Day 7, Day 14 and Day 21 study visits. An additional $50 will be given for completion of a biopsy at the Day 14 study visit. A total of $300 will be provided for completion of all study visits as compensation for their time and travel expenses.

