**6.3 Study Product Supply, Packaging and Accountability**

Instead Healthcare, LLC will provide Acidform lubricant, HEC gel and applicators for this study. Acidform lubricant and HEC placebo gel will be prepared in compliance with Good Manufacturing Practice (GMP) regulations for Instead Healthcare, LLC by Swiss-American Products, Inc, Carrollton, TX.

Study gel (Acidform or HEC) will be packaged in cartons containing 30 pre-filled plastic applicators. The AECOM Research Pharmacist will randomly allocate Acidform or HEC gel in a 1:1 fashion (i.e., 18 subjects per arm).

The pharmacist will maintain an accurate inventory and accountability record of study products received and subsequently dispensed. After the study is completed (or otherwise terminated), all unused study product will be shipped to Instead Healthcare, LLC for destruction. Participants will be dispensed thirty pre-filled applicators of study product at the Enrollment Visit. All product, used and unused, will be returned by the participants to AECOM or MMC. The subjects will be counseled that they are to apply 28 doses of drug or placebo. They will be instructed that they will be given 2 extra doses of drug or placebo to use only if a dose is dropped or lost.

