6.4 Assessment of Participant Adherence with Study Product/Intervention(s)

The first application of investigational product will be done at the Enrollment Visit by the participant under the guidance of the study clinician. Participants will be instructed to apply the assigned investigational product at bedtime and twice daily for 13 subsequent days (see Appendix III). For study visits conducted on Day 7 and 14, subjects will be instructed to apply the morning dose after the study visit is completed.

Participants will be asked to record information on the number of times they administer study gel, time of each insertion, and emergence/resolution of specific symptoms in a study diary. Diaries will be reviewed at each visit.

Non-adherence will be defined as three or more days (out of 14) of missed product use. Participants who miss less than three days will (if practical according to their expected date of menses onset) be asked to apply product for additional days to attempt to achieve a full 14 days of product exposure. An additional participant will be recruited for each non-adherent participant. Participants who are non-adherent with the study protocol will be asked their reasons for non-adherence and this information will be recorded on the applicable study forms. Study procedures for Day 7, Day 14, and the Final Visit will be re-scheduled as necessary. Participants will be instructed to call the study staff in the event of missed doses to re-schedule study visits.

Participants will be instructed to abstain from sexual relations throughout the course of the study. To assess whether intercourse occurred, a wet mount will be performed to look for sperm and a vaginal swab will be collected and tested for the presence of semen using the ABAcard p30 test. The test is an antibody immunoassay that detects p30, a glycoprotein produced by the prostate, which is present in human semen. p30 is detectable in the vaginal tract up to a maximum of 2 days. If a participant is found to have engaged in anal or vaginal sexual relations or experienced vaginal penetration with anything other than the study gel applicator throughout the study, this information will be recorded on applicable case report forms. Participants who are non-adherent to sexual abstinence on more than one occasion will discontinue product use. An additional participant will be recruited for each non-adherent participant.

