## Clinical Procedures

- Update locator information.
- Review interim medical history and concomitant medication information.
- Provide participant with screening test results.
- Collect urine for HCG pregnancy test; provide participant with result.
- Perform pelvic examination including:
- Speculum examination of vagina and cervix,
- Collect pH sample from the vaginal wall, anterior and posterior fornices,
- Gently swab anterior or lateral fornix for wet mount (two samples of discharge on slide for saline prep, potassium hydroxide prep, whiff test, and microscopic inspection for sperm) and p30 test for detection of semen,
- Collect vaginal swab for evaluation of vaginal flora,
- Collect cytobrush.
- If patient determined to be ineligible, end visit and complete all required data collection forms. If participant remains eligible, randomize/assign Enrollment ID and continue.
- Distribute study supplies, including thirty (30) single-application tubes of Acidform gel or placebo gel and 30 single-use applicators, study diary, application and storage instruction sheet (Appendix III) and panty liners.
- Instruct participants to bring study diary and used and unused tubes of gel to all follow-up visits.
- Provide information regarding product administration.
- Provide guidance for the administration of the first dose of study gel by the participant.
- Measure vaginal pH and collect CVL 2 hours post-application of Acidform or HEC.
- Instruct participant on anticipated amount, consistency and color of discharge due to gel expulsion.
- Instruct participant on proper gel insertion techniques and supply storage.
- Instruct participant to apply a dose at bedtime and then twice daily starting the next morning.
- Schedule Day 7 Study Visit.
- Instruct participant to not apply a dose on the morning of the Day 7 Visit. The dose will be applied after the study visit to avoid the effects of residual drug on study samples.
- Complete all required data collection forms and record any AE information.

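### The protocol orders a gel dose after the Day 14 cervical biopsy, although its 28-dose schedule ends at bedtime on Day 13

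*Protocol*

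**What the plan says.** **Dose total and schedule.** Section 6.3: "The subjects will be counseled that they are to apply 28 doses of drug or placebo". Thirty applicators are dispensed, and the two spares are reserved for a dropped or lost dose. Section 6.4, after the supervised clinic dose: "Participants will be instructed to apply the assigned investigational product at bedtime and twice daily for 13 subsequent days". The Enrollment Visit procedures in Section 7.1 confirm the Day 0 evening dose but give no end day: "Instruct participant to apply a dose at bedtime and then twice daily starting the next morning". Section 4.0 leaves that evening dose out: "the participants will insert subsequent applications twice daily for 13 consecutive days".

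**Dose after the visit.** Sections 4.0 and 6.4 both state: "For study visits conducted on Day 7 and 14, subjects will be instructed to apply the morning dose after the study visit is completed". The Day 7 procedures in Section 7.1 likewise have the participant hold the morning dose before the Day 14 visit and apply it afterwards.

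**The Day 14 visit.** Section 4.0 says the study clinicians "will collect one cervical biopsy colposcopically at the Day 14 visit for assessment of epithelial integrity". The Day 14 list in Section 7.1 includes the biopsy and disposal of remaining tubes, and gives no dosing instruction. The window is Days 12-15, with the aim of holding the visit after 14 days of dosing.

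**Missed days.** Under Section 6.4, women who miss fewer than three days will, if practical, "be asked to apply product for additional days to attempt to achieve a full 14 days of product exposure". The same paragraph adds: "Study procedures for Day 7, Day 14, and the Final Visit will be re-scheduled as necessary".

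**The concern.** The instruction to dose after the visit makes sense on Day 7, when a week of dosing is still to come. Carried over to Day 14, it conflicts with the dose total, with the last dosing day, and with the disposal of tubes at that visit. It also has the participant insert an applicator to about 6 cm and deposit 5 g of gel (Section 6.1) on the day her cervix was biopsied.

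Two things are at stake.

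- **Safety.** Section 2.3 lists pain, bleeding and infection as biopsy risks. Section 9.6 and Appendix IV stop product for treatment-related deep epithelial disruption and for ulceration. A biopsy is not product toxicity, but these rules show that gel on broken epithelium is a recognised concern. The screening biopsy is separated from the first dose by the next menses plus 2-6 days; the Day 14 biopsy has no such gap.
- **Attribution.** Relatedness is judged event by event (Section 8.1). It feeds the Grade 2 or higher related-event endpoint, compared by Fisher's exact test with 18 women per arm (Section 10.1), and the rule that two similar related grade 3 events in one arm suspend accrual (Section 9.5). Pain or bleeding after a biopsy and a gel dose on the same day is hard to assign to either.

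**Working it through.** **Inputs.** Total of 28 doses (6.3); clinic and bedtime doses on Day 0, then twice daily for 13 days (6.4, 7.1); Day 14 window of Days 12-15 (4.0, Appendix I); morning dose held on the visit day (7.1); Final Visit 3-8 days after the last dose (7.1) and within Days 16-21 (4.0, Appendix I).

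**Step 1: reproduce the stated total.** Day 0 gives 2 doses and Days 1-13 give 2 × 13 = 26. The total is 2 + 26 = 28, as Section 6.3 says, with dose 28 at bedtime on Day 13. Days 0 to 13 are also 14 dosing days, as Section 6.1 requires.

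**Step 2: cross-check the end day.** A last dose on Day 13 plus 3-8 days gives Days 16-21, exactly the stated Final Visit window. A last dose on Day 14 would give Days 17-22.

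**Step 3: Section 4.0 read alone.** 1 + 26 = 27 doses, one short of 28, also ending on Day 13.

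**Step 4: doses left at the biopsy, by visit day v.** With the morning dose held, doses taken = min(28, 2 + 2(v − 1)). Under the Section 4.0 count, doses taken = min(27, 1 + 2(v − 1)), set against the total of 28.

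| Visit day | Taken (6.3/6.4) | Scheduled doses left | Ordered after the biopsy | Section 4.0 count: taken, left of 28 |
|---|---|---|---|---|
| 12 | 24 | 4 | 4 | 23, 5 |
| 13 | 26 | 2 | 2 | 25, 3 |
| 14 | 28 | 0 | 1 (the 29th) | 27, 1 |
| 15 | 28 | 0 | 1 (the 29th) | 27, 1 |

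On Days 14 and 15 nothing scheduled remains, yet the text still orders one dose. Under the Section 4.0 count it would be the 28th, but it still follows the biopsy.

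**Step 5: make-up days.** One missed day means 2 doses, on Day 14. Two missed days mean 4 doses, on Days 14-15. If the visit moves to Day 15 or Day 16 respectively, 0 doses follow the biopsy. If it stays on Day 14, 2 or 4 follow it, and these include the Day 14 post-visit dose. With two missed days and a visit on Day 15, 2 follow it.

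**Step 6: does the fix fit the Final Visit rules?** Three rules apply: 3-8 days after the Day 14 visit, 3-8 days after the last dose, and Days 16-21.

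- No make-up, biopsy on Day 14: Days 17-21.
- One make-up day, biopsy on Day 15: Days 18-21.
- Two make-up days, biopsy on Day 16: Days 19-21.

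All three can be met in each case.

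**The case against.** **Section 4.0 may be coherent by itself.** Its 27 doses plus the post-visit dose make 28. The Day 14 list also counts 3-8 days to the Final Visit from the visit itself, which would match a last dose on the visit day. This shows how the text may have arisen. It does not remove the conflict: Sections 6.4 and 7.1 both specify the Day 0 bedtime dose, the Final Visit window fits a Day 13 end, and on either count the dose follows the biopsy.

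**For a visit on Day 12 or 13 the post-visit dose is a scheduled one.** That is correct, so the strict dose-count contradiction is one dose, for visits on Day 14 or 15. The earlier visits still put scheduled gel on the biopsy site.

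**Harm is not documented.** This stands. Nothing in the protocol shows that gel worsens biopsy outcomes, the cited irritation data are mild, and Appendix IV continues product on abrasions. Aftercare advice could sit in consent material that is not available here. Such advice would help the participant but would leave the protocol's three instructions in conflict with its schedule.

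**The comparison between arms is balanced.** This also stands. Both arms are biopsied and follow the same instruction.

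**A reader might infer that the make-up clause adds 2 or 4 further doses after the biopsy.** The text does not support that. The same paragraph re-schedules the Day 14 procedures as necessary, and Section 7.1 sets the visit by days of dosing. Those doses follow the biopsy only if the visit is not moved, and they include the Day 14 dose instead of adding to it.

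**Conclusion.** The conflict is real. Under Sections 6.3 and 6.4 dosing is complete at bedtime on Day 13, yet three places in the protocol order a dose after the Day 14 visit and its biopsy. The size is one unscheduled dose, the 29th, for a visit on Day 14 or 15. For a visit on Day 12 or 13 it is 4 or 2 scheduled doses. The counts assume that no dose is missed and that the morning dose is held on the visit day.

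The consequences are avoidable gel insertion on the day of a biopsy and harder attribution of individual adverse events. Neither can be quantified from the document. The Day 21 lavage might be affected, but that cannot be shown either. A reader might go on to infer that the mucosal endpoints or the epithelial-integrity result are contaminated. They are not by this route, because the Day 7 and Day 14 samples and the Day 14 tissue are all taken before any post-biopsy dose. This is a participant-safety and clarity correction that should be made, not a threat to the primary comparison.

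**What to change.** 1. **Sections 4.0 and 6.4:** limit the dose-after-visit sentence to Day 7.
2. **Section 7.1, Day 7 procedures:** keep the morning hold before the Day 14 visit, but delete the sentence ordering the dose afterwards.
3. **Section 7.1, Day 14 procedures:** add 'Instruct participant to stop gel; no gel is inserted after the Day 14 biopsy.' Naming the Day 14 biopsy avoids confusion with the screening biopsy.
4. **Section 4.0, enrollment paragraph:** add the Day 0 bedtime dose so that this section also totals 28.
5. **Section 6.4:** state that make-up days are completed before the Day 14 biopsy visit, which is re-scheduled accordingly.
6. **Section 4.0, Section 7.1 and Appendix I:** hold the biopsy visit on Days 14-15, so that all 28 doses come first. A later day, such as Day 16 after two make-up days, lies outside the present window and should be allowed only through the Section 6.4 re-scheduling clause.

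No visits, samples or participants are added, and an on-schedule woman still receives all 28 doses. The cost is a window cut from four days to two, apart from make-up cases. If Days 12-13 are kept for women who cannot attend later, stopping at the biopsy leaves them with 24 or 26 doses. The protocol should then say how those undosed days count under its non-adherence rule.

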**4.1 Laboratory Methods**

The vaginal pH will be measured using an electronic ISFET pH meter. A stainless steel sensor pH probe will allow us to measure the pH in different locations in the vagina. There is less variability with the probe compared to pH paper, which has been used in most of the previous studies. We will measure pH at Screening, Enrollment (prior to and 2 hours after the first application of Acidform or HEC), Day 7, Day 14 and Day 21.

CVL will be immediately transported on ice to the investigators’ laboratories and centrifuged for 20 minutes at 1000 g at 4C, aliquoted and stored at -80C. CVL will be collected using 10 ml of normal saline. We have demonstrated that Acidform gel retains its low pH (~ 3.5) when mixed 1:10 with normal saline. Thus, collection of CVL in normal saline should not interfere with the buffering effects of Acidform. Cytobrush specimens will be transported on ice to the lab. The cells will be gently dislodged, centrifuged and immediately frozen in fetal bovine serum with 10% dimethyl sulfoxide. The cells will be thawed at a later date, counted, washed, respun and stained using a panel of differentially conjugated mAbs against various human leukocyte membrane antigens and analyzed by fluorescent activated cell sorter (FACS). Cell preparations will be labeled in parallel with appropriate isotype control Abs (Becton-Dickinson).

Cytokines and chemokines in CVL supernatants will be quantified using a multiplex Luminex assay (Millipore), which allows for the quantitative measurement of multiple cytokines or chemokines using a small sample size. The following mediators will be measured by Luminex: IL-1, IL-1, IL-2, IL-6, IL-8, IFN-, IFN-, and RANTES. IgG, IgA, SLPI, IL-1ra, lactoferrin, lysozyme and HNP1-3 also will be measured using commercial ELISA kits (R & D Systems, Minneapolis, MN). These mediators were selected because of their potential to influence mucosal immunity. The total protein concentration will be measured and the results will be presented per mg of protein in CVL as well as per ml of CVL to control for any differences in CVL collection. To determine whether Acidform or HEC interferes with the detection of any of the mediators, standards will be diluted in saline or saline containing Acidform or HEC gel (2 ml of Acidform or HEC added to 10 ml of normal saline) and results will be compared.

CVL will be assayed for endogenous antimicrobial activity, focusing on the ability of CVL to inhibit HSV and *E. coli*. HSV and *E. coli* were selected based on prior studies from our laboratory. For the endogenous anti-herpes activity, human cervical epithelial cells (CaSki) will be treated with each CVL sample or control buffer (normal saline containing 2 mg/ml of albumin to control for total protein concentration) and then challenged with serial dilutions of HSV-2(G) in duplicate. The ability of the CVL to inhibit viral infection will be determined by comparing the viral titer (pfu/well) in the presence of each CVL sample to that in the presence of control buffer and will be determined by counting plaques 48 h post-infection. The effects of CVL pre- and post-application of Acidform or HEC gel on the growth of *Escherichia coli* ML-35 will also be examined.Serial dilutions of the bacteria will be incubated with an equivalent volume of CVL or control fluid at 37C for 2 h before plating on agar plates. Colonies will be counted using ImageQuant TL v2005 after an overnight incubation at 37C and relative number of colonies will be compared. It should be noted that the CVL is collected ~10-12 hours post-application of Acidform or HEC and thus the antimicrobial activity should primarily reflect changes in innate immunity, rather than the direct effects of the gel. However, a contribution from residual gel cannot be excluded.

To assess the activity of the gels themselves, we will compare the antiviral activity of Acidform or HEC in CVL obtained 2 hours after the first application using a spiking strategy. The experimental design is based on our prior studies with 0.5% PRO 2000 gel (12). Serial dilutions of each CVL supernatant will be spiked with dilutions of HIV-1 or HSV-2 (diluted in saline or seminal plasma), assayed for pH and then inoculated onto susceptible cells. For HIV, we will use TZM-bl cells expressing CCR5 or CXCR4 and CD4 and infect with the appropriate R5 or X4 viruses. For HSV-2 studies, we will use a human cervical epithelial cell line. The viral titer will be determined by counting plaques 48 h post-infection after immunostaining by black plaque assay. Seminal plasma collected from low risk males who participated in a previous unrelated study will be used for these experiments. These studies will also be expanded to include primary isolates representative of different clades and primary cell cultures.

To assess epithelial integrity, cervical biopsy specimens will be split into two sections. One half will be used for confocal studies and the other half for real-time PCR studies. The biopsy tissue will be stained with EZ-Link sulfosuccinimidobiotin reagent, which reacts with primary amines on cell-surface proteins. Following membrane labeling, the tissue will be fixed with paraformaldehyde. To visualize junctional proteins, the tissue will be permeabilized with 1% Triton X after fixation, incubated with the appropriate primary Abs and subsequently with an Alexa Fluor 488-conjugated anti-mouse secondary Ab. Nuclei will be detected by staining with DAPI nucleic acid stain. Imaging studies will be conducted in the Microscopy Core Facility. The other half of the biopsy sample will be homogenized and total RNA extracted and levels of mRNA transcripts determined by quantitative real-time PCR. Expression levels of cellular architectural proteins including E-cadherin, ZO-1, nectin, and others will be determined using established primer and probe sequences with the inclusion of an appropriate housekeeping gene as an endogenous control.

We will also compare differences in vaginal flora pre- and post-application of Acidform lubricant and HEC gel. Vaginal swabs will be collected at Enrollment, Day 14 and Day 21, stored at -80, batched and transported to [name] laboratory at the Fred Hutchinson Cancer Research Center for analysis. Briefly, the vaginal swabs will be diluted in saline, vortex mixed, and centrifuged at 14,000 g for 10 minutes and DNA will be extracted from the pellet using the Ultra Clean Soil DNA Kit (MoBio). Taxon-directed real time quantitative 16S rRNA gene PCR assays will be utilized to detect and quantify *Lactobacillus crispatus*, *Gardnerella vaginalis*, *E. coli*, and BVAB1, BVAB2 and BVAB3 using a modification of previously described assays that have been validated in the lab (16, 17). These assays employ a fluorescent TaqMan probe to monitor production of the intended bacterial 16S rDNA product with each PCR cycle, allowing construction of a standard curve based on known quantities of bacterial 16S rDNA, and the calculation of bacterial concentrations in vaginal samples. Organisms were chosen to target bacteria commonly found in healthy women (*L. crispatus*, *G. vaginalis*, *E. coli*). In addition, we selected organisms specific to BV (BVAB1-3) given the possibility of encountering asymptomatic BV or altered flora in the proposed clinical study.

